##### Statistical analyses

Following an intention-to-treat principle, clusters will be analyzed according to their randomized crossover time regardless of whether crossover was achieved at the desired time. We will use a generalized linear mixed model (GLMM) in our analysis. This approach employs a random-effect term to account for multiple correlated visits for each pulmonologist (cluster), as well as other available covariates to adjust for potential confounders. Given the binary nature of the primary endpoint (prescription appropriateness), we will use a logistic GLMM. For our secondary outcomes, we will examine different standard continuous distributions in the GLMM to find the best fit to the data (according to the major goodness-of-fit measurement, such as Akaike information criteria [AIC], quasi-information criterion [QIC], and prediction error). The same approach will be used to find the optimal distribution and correlation structure of the GLMM analysis for each outcome. Additionally, time will be added as a fixed effect to capture trends in the outcome over the course of the study (steps) [44, 48]. Lastly, we will use multivariate imputation by chained Eqs. [49] to impute all missing values in the data that can be considered missing at random. All analyses will be adjusted for patient covariates to account for chance group imbalance. A sensitivity analysis will also be conducted that involves not adjusting for covariates (other than time of switch and cluster).

To test the sex- and gender-related hypotheses, we will conduct a principal component analysis in which gender-sensitive variables (Supplementary Material — Sect. 1) are combined into a scalar “gender index” [50]. To examine the effect of this index on the accuracy of risk prediction, we will use established statistical methods to examine the incremental value of a new predictor (improvement in c-statistic, bias-corrected net reclassification index, and decision curve analysis) [51].

For qualitative data analysis, interviews will be audio-recorded and transcribed, in addition to detailed note-taking throughout the interviews. The transcripts will be uploaded to NVivo 12 for analysis. The interviews will be analyzed using both inductive and deductive content analysis methods [52]. We will employ the TTT to guide the interviews, whereby questions are aimed at understanding barriers and facilitators to uptake and implementation of the tools. We will also employ the TTT to analyze the results of the interviews. For example, if a patient states that they feel they have improved skills to manage their COPD because of the instruction received, then we would deductively map this onto the appropriate TTT constructs. We will also inductively analyze interview data to capture contextual experiences described by the participants. We will disaggregate the data by sex (female/male) to accommodate possible differences in experiences. Two researchers will iteratively engage in the process of qualitative data analysis to ensure that a cohesive framework is achieved.

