Outcome 3	Rate of moderate/severe exacerbations	Moderate exacerbations: Any outpatient physician visit for COPD followed by filling prescriptions for antibiotic or oral corticosteroids Severe exacerbations: A hospital admission with the main discharge code of COPD	Change in rate of moderate/severe exacerbations	The departure from guideline-base care is a mixture of over- and undertreatment, and the proposed intervention is likely to reduce such departure from guidelines. Correcting undertreatment will reduce exacerbation rate, while correcting overtreatment will not materially change the rate, resulting in a net-reducing effect. In addition, improving adherence will further reduce exacerbations
Outcome 5	Impact of COPD on health status	Measured by the COPD Assessment Test (CAT) [34]. The CAT includes 8 questions scored from 0 to 5, with higher scores indicating more severe impact of COPD	Improved health status	Patient-reported outcomes are likely to be affected by a quality-improvement intervention that involves addressing low health literacy and inaccurate medication beliefs [35]
Outcome 6	Quality of life	Euro Quality of Life-5 Dimensions (EQ5D). The EQ5D is a standardized questionnaires that assess 5 dimensions of health status, each at 3 distinct levels [36]. These data will be used to track changes in patient-report quality of life over the duration of the study	Improved quality of life	Patient-reported outcomes are likely to be affected by a quality-improvement intervention that involves addressing low health literacy and inaccurate medication beliefs [35]

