Outcome 7	Smoking cessation	Measured by the following questions 1. Smoking status will be assessed by asking, “Do you currently smoke cigarettes” (yes/no)? 2. Motivation to quit will be assessed using the motivation to stop smoking (MTSS) scale [37]. Participants will be asked to classify themselves into one of the following six stages: (a) I do not want to quit smoking, (b) I think I should stop smoking but do not really want to, (c) I want to stop smoking but have not thought about when, (d) I REALLY want to stop smoking and intend to in the next 3 months; (e) I want to stop smoking and hope to soon, (f) I REALLY want to stop smoking and I hope to in the next month 3. Nicotine dependence will be assessed using the Fagerström test [38]—a questionnaire made up of 7 questions, the first scored as 0 and 1 (yes/no), and the remaining 6 multiple-choice questions scored from 0 to 3. The total test score ranges from 0 to 10, with higher scores indicating more intense physical dependence on nicotine 4. Cessation methods will be assessed by asking: Which of the following methods have you tried in the last 6 months (check all that apply): (a) nicotine replacement therapy, (b) cold turkey, (c) Champix®, (d) bupropion (Wellbutrin or Zyban), and or (e) behavioral support (e.g., smokers help line, cessation support group, cessation website, smartphone app)	Improved lifestyle behaviors	While smoking cessation is recommended for all current smokers with COPD, very few are offered such an intervention. Studies have suggested that even a brief intervention can be effective on reducing exacerbation rates [39]

*ACCEPT* Acute COPD Exacerbation Prevention Tool, *BMQ* Beliefs about Medicines Questionnaire, *CAT* COPD Assessment Test, *COPD* Chronic obstructive pulmonary disease, *EQ5D* EuroQoL 5-dimension, *MTTS* Motivation to Stop Smoking scale

We chose “prescription appropriateness” as the primary endpoint because it is the process of care outcome that is most directly affected by the intervention, and it has been frequently used in trials on computerized decision support tools [33]. Prescription appropriateness will be assessed by determining the concordance between the pulmonologist- and CTS-based treatment recommendations.

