##### Data collection

The total duration of the trial is 30 months. Initially, all participating pulmonologists will be in the comparison arm. After 6 months, two randomly selected pulmonologists will be reassigned to the intervention arm every other month (Fig. 2). In month 18, the last two pulmonologists will be assigned to the intervention arm, and patient recruitment will continue until month 24. Follow-up data will be collected until month 30 to ensure 6 months of follow-up data for all patients.

To assess the primary endpoint, the prescribed versus recommended treatments will be automatically documented and collected in aggregate form under a unique identification (ID) code assigned to each pulmonologist. If a patient consents to the longitudinal component, a baseline study visit will be conducted that includes administration of questionnaires to collect clinical and patient-reported data to assess secondary outcomes (Fig. 4). Subsequently, two follow-up appointments will be arranged at 3- and 6-month post initial visit via telephone. If a patient sees an enrolled pulmonologist multiple times throughout the 24-month study period, the first visit with the pulmonologist will be used to mark the start of the follow-up period for longitudinal data collection, unless the pulmonologist was reassigned to the intervention arm between visits. In this case, if the patient has consented to the longitudinal component, the follow-up period will be reset during the first visit the pulmonologist is in the intervention arm, and the patient will be followed for another 6 months after the initial intervention arm visit.

To deliver the intervention package, site coordinators will set up automatic software triggers for all eligible patients seeing a pulmonologist allocated to the intervention arm. A trigger will launch when the pulmonologist opens a patient’s EHR chart during the patient encounter, and the ADI will be pre-populated with predictor values. If a predictor value is not retrieved from a patient’s EHR, the empty fields will be highlighted and will be fillable through dictation or by typing directly into the ADI computer interface. At the end of the encounter, the pulmonologist will print the customized patient tool that will be distributed by the research coordinator.

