#### Data analyses

##### Sample size calculations

Details of the sample size calculation is provided in the Supplementary Material — Sect. 2. In summary, the sample size is based on a formula for a stepped-wedged cluster RCT under a cross-sectional sampling method [44, 45], accounting for the variance in inflation due to the intra-cluster correlation and an adjustment for unequal cluster sizes. Sample size calculation was based on a type 1 error of 0.05 and a power of 80%. The current rate of prescription appropriateness was based on our analysis of BC’s administrative health data [46]. The unadjusted sample size was estimated to be 528 per arm.

The design effect is a function of the overall design features (i.e., the cross-over feature, number of clusters, run-in period), as well as the intra-cluster coefficients and cluster autocorrelation. These were obtained from a dedicated analysis of administrative health data from BC using prescription patterns from all physicians in the province [46]. The estimated intra-cluster coefficients and cluster autocorrelation were 0.026 and 0.491, respectively, resulting in a design effect of 2.15. Finally, the design effect was further adjusted for unequal cluster sizes [47], giving rise to a value of 2.18. Based on these, the total sample size is: 528 × 2.18 $$\approx$$ 1153.

To test the feasibility of achieving this sample, we performed an audit of the 2019–2020 fiscal year in one of the study sites and recorded 5559 visits. We estimate 17% of visits are due to COPD and eligible for this study. Given patient traffic in this site is expected to contribute to 60% of the overall traffic, and the 2-year recruitment window, the expected total number of eligible patients will be 3024. Therefore, to achieve the desired sample size, we will need to obtain the primary endpoint for 38% of the visits, a figure that we consider achievable given our experience with clinical studies at both sites.

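### The secondary outcomes are confined to continuous distributions chosen by fit, which is the wrong family for exacerbation counts and yes/no smoking items and unsuited to the six-stage motivation item

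*Protocol article*

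**What the plan says.** The Statistical analyses section specifies a generalized linear mixed model (GLMM) throughout. The primary endpoint gets a logistic version because it is binary. The rest are covered by one sentence: "For our secondary outcomes, we will examine different standard continuous distributions in the GLMM to find the best fit to the data". The criteria named are AIC, QIC and prediction error. The following sentence extends the same selection to the distribution and the correlation structure for each outcome. The one random effect that is named belongs to the pulmonologist: "This approach employs a random-effect term to account for multiple correlated visits for each pulmonologist (cluster").

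Table 1 under Study outcomes includes:
- Outcome 3, "Rate of moderate/severe exacerbations", built from physician visits followed by a filled prescription and from hospital admissions.
- Outcome 7, which holds a yes/no item ("Do you currently smoke cigarettes"), a six-stage motivation scale, the Fagerström score and a tick list of cessation methods.
- The medication possession ratio, the Beliefs about Medicines Questionnaire (BMQ), the COPD Assessment Test (CAT) and the EQ5D.

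Under Data collection, the baseline visit is followed by further contacts: "two follow-up appointments will be arranged at 3- and 6-month post initial visit via telephone". A consented patient seen again after the pulmonologist has switched starts a new six-month follow-up.

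**The concern.** An article may leave model details to the analysis plan. Here, though, it does not leave the distribution open: it names a class, and the class is wrong for some of the outcomes it covers. If followed literally, the exacerbation rate would be analysed with a model that either cannot accept patients without events or assumes a constant variance that counts do not have. The smoking items would be handled differently from the binary primary endpoint, without a reason.

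Exacerbations are the clinical outcome that the intervention is ultimately meant to change, and the Discussion already says that the trial is under-powered for them. A poorly fitting model would make a weak comparison harder to interpret.

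A second, smaller matter is repeated questionnaires on the same patient. No patient-level term is named, and whether one enters depends on selection by fit.

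**Working it through.** **1. The plan's own figure.** 528 × 2.18 = 1151.04, against a stated total of 1153 (1153 / 528 = 2.184, so the gap is rounding of 2.18). This checks only the printed product. The figure concerns the binary primary endpoint and does not change with anything below.

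**2. Outcome type against the stated class.**

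| Secondary measure | Type | Continuous family suitable? |
|---|---|---|
| Moderate/severe exacerbations | Event count | No |
| Current smoking | Binary | No |
| Each cessation method | Binary | No |
| Motivation to stop | Six ordered stages | Poorly suited |
| Medication possession ratio, CAT, BMQ, EQ5D, Fagerström score | Ratio or score | Yes, reasonably |

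**3. Exacerbation counts.** The article gives no expected rate, so the mean μ per patient and window (0.25 to 1.5) and the dispersion k (0 to 1) are assumptions. The share of patients with no event is exp(−μ) for a Poisson count and (1 + kμ)^(−1/k) for a negative binomial.
- μ = 0.25: exp(−0.25) = 0.779; with k = 1, 1/1.25 = 0.800.
- μ = 1.5: exp(−1.5) = 0.223; with k = 1, 1/2.5 = 0.400.

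So 22% to 80% of patients would have a zero. Gamma and log-normal distributions have no probability at zero. A Gaussian model accepts zeros but assumes one variance. With k = 1 the variance μ + kμ² is 0.3125 at μ = 0.25 and 3.75 at μ = 1.5, a twelvefold difference across the assumed range.

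**4. Repeated questionnaires.** Suppose two follow-up records per patient were pooled as independent, under one condition, with within-patient correlation ρ (assumed 0.3 to 0.8). The standard error is then too small by √(1 + (2 − 1)ρ), and the true level of a nominal 5% test is 2(1 − Φ(1.96 / that factor)).
- ρ = 0.3: √1.3 = 1.140; level 8.6%.
- ρ = 0.8: √1.8 = 1.342; level 14.4%.

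This is an upper-end illustration, because it assumes that no patient-level correlation enters the model at all.

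**5. The primary model and the autocorrelation.** Planning used these values: "The estimated intra-cluster coefficients and cluster autocorrelation were 0.026 and 0.491". The check took them as true, fitted a working model with a pulmonologist intercept only, and compared true with model-based standard errors (linear approximation, run-in month left out). Two layouts were used, each with two pulmonologists per step: twelve monthly steps and seven two-monthly steps. Each was run with 1153 and 2306 observations. The ratio of true to model standard error was 0.99 to 1.03, and the type I error 4.9% to 5.8%.

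**The case against.** The best defence has four parts.

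First, the wording suits most secondary measures, and a Gaussian fit to a count or a yes/no item estimates a rate or risk difference, which is a legitimate scale. That is fair, and no claim is made here that such an estimate is biased in a given direction. But the plan does not state a difference scale as its aim. It says that the best-fitting continuous distribution will be used.

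Second, selection by fit might be expected to correct the family. It cannot, because every candidate is continuous. Adding count models to the pool would not settle it either, since AIC does not put a density and a probability mass on a common footing.

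Third, person-time matters little. Administrative data are requested for a uniform year before and after the baseline visit, so exposure is nearly constant. This stands, and it limits the offset to patients whose observation is incomplete.

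Fourth, a reader might infer that the plan is fixed to a single pulmonologist effect and so excludes a patient term. The documents do not support that: the sentence after the one quoted leaves the correlation structure to be found for each outcome. For the same reason the 9% to 14% is not a forecast, and a fit criterion might well pick up the correlation. A larger figure of 12% to 22% follows if three records are counted, but that treats baseline as an outcome. Patients whose follow-up is reset contribute to both conditions, so part of their comparison is within patient, and ignoring correlation there need not understate the variance.

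A reader might also infer that the planning autocorrelation has been dropped from the primary model in a way that matters. The term is not named, but at the stated values leaving it out moves the error rate only to about 5% to 6%.

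**Conclusion.** The distribution rule is wrong as written for the exacerbation rate, smoking status and each cessation method, and unsuited to the motivation item. It is also inconsistent with the reason given for the logistic primary model. This part rests on the article's text alone; only the share of zeros (22% to 80%) depends on assumed rates.

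The missing patient term is a lesser point: it should be fixed in advance, but it is unspecified rather than excluded, and the 9% to 14% rests on assumed correlations and on complete pooling. No material error is established for the primary model. The consequences are confined to secondary outcomes, so this is a correction that should be made rather than a threat to the main inference.

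**What to change.** Replace the sentence on continuous distributions with a family set by outcome type:
- Exacerbations: negative binomial (or Poisson allowing for overdispersion) with log link, and a log follow-up-time offset where follow-up is incomplete.
- Smoking status and each cessation method: logistic.
- Motivation to stop smoking: an ordinal model.
- Medication possession ratio, CAT, BMQ, EQ5D and Fagerström score: continuous distributions, as now.

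For consented longitudinal outcomes with more than one record per patient (3 and 6 months, and patients whose follow-up is reset after the switch), state in advance a patient random effect within pulmonologist, and do not leave it to selection by fit. This cannot extend to the primary endpoint, whose data are collected without patient identifiers.

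The cost is analysis wording. No data collection or sample size changes. Intervals for the repeated questionnaire outcomes will be somewhat wider than if records were pooled as independent: at most the 14% to 34% implied by the factors 1.140 and 1.342 above.

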#### Study population

Since the intervention will be embedded into the EHR as a standard clinical decision support system and will be part of routine care, all staff pulmonologists at the two study sites (*n* = 28) will participate automatically in the study. However, conservatively anticipating data from the practice of four physicians will not be used for this study for various reasons, such as an extended leave; we aim to use data from 24 pulmonologists, who will comprise the study clusters. Individual patients who are referred to one of the participating pulmonologists at a study site with a physician-assigned diagnosis of COPD will be invited to participate in the clinical trial. For inclusion, individuals must be as follows: (1) a legal Canadian resident, (2) aged 18 years and older, and (3) able to understand English.

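### As worded, the primary model's correlation structure is chosen by fit to the outcome data, so the primary test is not fixed in advance, although the expected error inflation is small

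*Protocol article*

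**What the plan says.** Under Statistical analyses, the protocol article names a GLMM with a random-effect term for pulmonologist, time as a fixed effect and patient covariates. For the binary primary endpoint the model is logistic. For the secondary outcomes, continuous distributions are to be compared by goodness of fit, with these measures given as examples: "Akaike information criteria [AIC], quasi-information criterion [QIC], and prediction error". The next sentence widens the rule: "The same approach will be used to find the optimal distribution and correlation structure of the GLMM analysis for each outcome". The section gives no ranking of the criteria, no list of candidate structures and no default. The one sensitivity analysis described there removes patient covariates and leaves the correlation structure alone.

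Under Sample size calculations, the correlation structure is specific: "The estimated intra-cluster coefficients and cluster autocorrelation were 0.026 and 0.491, respectively, resulting in a design effect of 2.15". Under Study population, the number of clusters is set: "we aim to use data from 24 pulmonologists, who will comprise the study clusters".

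**The concern.** This is a stated rule, not a detail left to the SAP: an SAP must either follow it or depart from it. The logistic distribution of the primary is settled, but its correlation structure is not, and fit criteria can be computed only from the outcome data. Three things follow.

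- The primary p-value and interval come from whichever structure wins. The criteria can disagree, and nothing says which prevails or that the choice is made without sight of the treatment effect.
- QIC rests on the quasi-likelihood used in GEE. It is not defined for the likelihood-based GLMM that the plan names, so that part of the rule cannot be applied as written.
- AIC and prediction error reward parsimony and prediction, not a correct standard error for the treatment effect. An autocorrelation well below 1 means that two visits to the same pulmonologist are less alike in different periods than in the same period. The sizing treats this pulmonologist-by-period variation as real, yet a fit-based rule may discard it.

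**Working it through.** **1. The plan's own figure.** The article states: "The unadjusted sample size was estimated to be 528 per arm". It then reports that "the design effect was further adjusted for unequal cluster sizes [47], giving rise to a value of 2.18". 528 × 2.18 = 1151.04, against a stated 1153; since 1153/528 = 2.184, the gap is rounding. The 528 cannot be rebuilt, because the article gives no rates.

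**2. The structure behind the sizing.** The nested-exchangeable stepped-wedge design effect, with m visits per cluster-period, L steps, ICC ρ and autocorrelation π, is

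(L + 1) × [1 + (m − 1)ρ] × 3L(1 − r)(1 + Lr) / [(L² − 1)(2 + Lr)], where r = mρπ / [1 + (m − 1)ρ].

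With ρ = 0.026 and π = 0.491 from the article, and m = 5 and L = 12 assumed:
- 1 + 4 × 0.026 = 1.104
- r = 5 × 0.026 × 0.491 / 1.104 = 0.0578
- the last factor = 0.149
- the product = 13 × 1.104 × 0.149 = 2.14

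This is close to the stated 2.15, so the sizing is consistent with a model that has both pulmonologist and pulmonologist-by-period effects. With total variance 1, the components are:
- pulmonologist: 0.026 × 0.491 = 0.0128
- pulmonologist-by-period: 0.026 × 0.509 = 0.0132
- residual: 0.974

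**3. Would AIC keep the component?** Two null simulations with 24 clusters and these components:
- *Simulation A:* 2000 trials per scenario, Gaussian outcome, 12 two-month or 13 equal periods. AIC kept the term in 7–9% of trials at 1153 visits (the target) and about 30% at 3024 visits (the article's count of eligible patients).
- *Simulation B:* 4000 trials per scenario; binary outcome near 50%, analysed by a linear mixed model with month effects; two clusters crossing per month in months 7–18; run-in month dropped. Four candidates: random intercept; plus cluster-by-period; exponential decay; plus random treatment effect. AIC chose the true nested structure in 4.1% of trials at 1104 visits and 9.6% at 2760. It chose the plain random intercept in 85.7% and 78.4%.

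**4. What that does to a nominal two-sided 5% test.** In simulation A, rejection rates were 5.8–6.8% with a fixed structure and 6.0–7.0% with AIC choice (Monte Carlo SE about √(0.05 × 0.95/2000) = 0.5 points). Simulation B, z test, SE about √(0.05 × 0.95/4000) = 0.34 points:

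| True correlation | Visits | Matching structure fixed | Chosen by AIC | Most favourable of four | Plain random intercept |
|---|---|---|---|---|---|
| Article's ICC and autocorrelation, monthly | 1104 | 5.4% | 5.5% | 5.7% | 5.6% |
| Same | 2760 | 5.2% | 5.4% | 6.2% | 5.9% |
| ICC 0.10 (assumed), autocorrelation 0.491 | 1104 | 4.4% | 4.7% | 4.9% | 4.8% |
| ICC 0.026, decay 0.9 per month (assumed) | 1104 | 5.1% | 5.2% | 5.8% | 5.6% |
| Same | 2760 | 5.2% | 5.5% | 7.5% | 7.3% |
| ICC 0.10, decay 0.9 per month (assumed) | 1104 | 5.6% | 5.8% | 8.5% | 8.4% |
| Article's values plus effect varying by cluster (assumed) | 1104 | no exact match | 5.1% | 6.0% | 5.7% |
| Same | 2760 | no exact match | 6.1% | 7.6% | 7.4% |

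**5. Standard error if the component is dropped.** With one- to two-month periods it is about 1–5% too small. At the upper end the true error is 2Φ(−1.96 × 0.95) = 6.3%; at 1% it is 2Φ(−1.96 × 0.99) = 5.2%.

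**The case against.** **Scope.** The sentence follows one about secondary outcomes and pairs distribution with correlation structure, while the primary's distribution is already settled. A reading confined to secondary outcomes is possible. It stands as a possibility, but the authors limited the preceding sentence to secondary outcomes explicitly and did not limit this one. If that was the intent, a single clause is still needed.

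**Size.** Mechanical AIC choice hardly moves the error rate. In simulation A the difference from a fixed structure is within Monte Carlo error, and the excess over 5% is already there with the structure fixed. This stands, and it bounds the point.

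**Stronger readings.** A reader might infer that naming QIC admits GEE fits with uncorrected robust errors, and hence a much larger inflation. The article commits to a GLMM and proposes GEE nowhere, so that is not supported. A reader might also infer from AIC's low retention that standard errors would be badly understated. That would need correlation periods far longer than the two-monthly switching under Data collection; the article does not give the period to which 0.491 refers.

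**Omission.** A ranking of criteria or a small-sample reference may properly sit in the SAP. True of those details taken alone. The finding is the selection rule that the article does state.

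**Conclusion.** The point holds in a limited form. As worded, the correlation structure of the primary model is open to choice after outcomes are seen, under criteria that are unranked and in one case unsuited to the model. AIC would usually leave out the variance component implied by the sizing. It does not follow that the trial's 5% level is seriously breached: the cost of applying AIC mechanically is about 0–1 point. The larger exposure is the freedom to choose among structures: about 6% under the article's inputs, up to about 8.5% under assumed persistent correlation with an ICC of 0.10.

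These figures rest on Gaussian or linear approximations, an assumed base rate and assumed layouts. A layout had to be assumed because two pulmonologists every other month from month 6 to month 18 makes 7 × 2 = 14 switches, not 24. Selection by QIC or prediction error was not simulated. That the test is not fixed in advance depends on none of these assumptions.

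**What to change.** Amend Statistical analyses before outcome data are seen:

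- Exempt the primary outcome from fit-based selection and name one model, kept whatever AIC says: a logistic GLMM with fixed period effects, random pulmonologist and pulmonologist-by-period effects, and a small-sample (t) reference for 24 clusters. Define the period as in the sizing.
- Limit fit-based choice to the secondary outcomes and delete QIC.
- Report other correlation structures for the primary only as labelled sensitivity analyses.

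This needs wording only and no new data. The named model may fit slightly less well and its interval may be a few percent wider. The t reference can be mildly conservative: with 22 degrees of freedom, the nested model in simulation B rejected in 4.4% (1104 visits) and 4.0% (2760 visits) of null trials under the article's correlations.
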